### Study Intervention

#### Usual Diabetes Care

The control group received the standard of diabetes care in the RMI, which consisted of the standard treatment protocols used by the MOH Diabetes Clinic. These included placing T2D patients on anti-hyperglycemic agents appropriate to their HbA1c levels (including sulfonylureas, metformin, and insulin) and providing oral and written information about the importance of maintaining a healthy weight, eating a healthy diet, and getting regular exercise. Participants in the control group were instructed not to make changes in their diet and activity levels during the study.

#### Lifestyle Intervention

The lifestyle intervention consisted of a high-fiber, low-fat, mostly plant-based diet, and moderate exercise. Participants initially received 12 weeks of group educational classes and meals prepared by the DWC Wellness Kitchen and then followed the lifestyle intervention on their own for the remaining 12 weeks (Table 1). Group classes included informative sessions on healthy eating, exercise (both aerobic and strength training), and stress management, as well as hands-on cooking classes. Classes were delivered as a combination of PowerPoint presentations, practical workshops, dine-outs, shopping tours, and cooking classes with spouses. To foster access to affordable produce, participants were also taught by soil and gardening experts how to grow their own vegetables and were taken on agricultural field trips.

**Table 1 T1:** Standard and enhanced versions of the intensive lifestyle intervention.

**Standard version**	**Enhanced version**	**Frequency**	**Meals/day**	**Group classes**	**Exercise**
Weeks 1–2	Weeks 1–2, 4, and 6	4 days/week	3	5–6 h	1 h
Weeks 3–6	Weeks 3 and 5	2 days/week	1	4–5 h	30–60 min
Weeks 7–12	Weeks 7–12	1 day/week	1	4–5 h	30–60 min
Weeks 13–24	Weeks 13–24	1 day/week	0	Turn in Pedometer Readings	

*The standard and enhanced versions of the lifestyle intervention differ only during weeks 4 and 6*.

The initial 12-week program was structured as follows. During the first 2-week intensive phase, participants in all cohorts attended 5–6 h/day of group classes on Mondays–Thursdays (4 days/week) at the DWC, totaling 36 h of health education over the first two weeks. Figure 1 displays the schedule for the intensive phase. On clinic days, group sessions included 1 h/day of exercise, and participants were fed 3 meals/day made by the DWC Kitchen, according to the menus shown in Table 2. Participants ate breakfast at the DWC and took lunch boxes with them to eat at work or at home. The participants then returned to the DWC for a 5-h session from 3:00 to 8:00 p.m., where they helped prepare the meals and then ate dinner. Participants prepared the main dish, and the kitchen staff made the side dishes (e.g., green salad). During weeks 3–6, participants who received the standard version of the intervention (Cohorts 1–2) spent 4–5 h twice per week (Tuesdays and Thursdays) in group sessions, including 60 min/day of structured exercise, a 10–20-min walk after each meal, and also consumed an evening meal provided by the DWC Wellness Kitchen (see menus in Table 3). For those receiving the enhanced version of the intervention (Cohorts 3–5), weeks 4 and 6 of the standard intervention were replaced with weeks 1 and 2 to increase the intensity of instruction, as shown in Table 1. During weeks 7–12 of the program, participants in all cohorts participated in a 4–5 h once per week session with structured exercise and group classes and were provided an evening meal. Finally, during the last 12 weeks of the trial (weeks 13–24), no instruction or counseling was provided, and participants came to the center weekly to turn in their pedometer readings.

**Figure 1 F1:**
[figure not shown]
Schedules for the first 3 weeks of the lifestyle intervention.

**Table 2 T2:** Study menus for weeks 1–2.

	**Breakfast**	**Lunch**	**Dinner**
**WEEK 1**			
Monday	Not provided	Salad bar Sesame tahini dressing Pumpkin and/or breadfruit and red bean salad Cream of broccoli soup	^*^Crispy tofu fingers ^*^Spicy eggplant Fresh fruit or vegetables
Tuesday	^*^Pineapple and coconut muesli ^*^Beans and greens Ground flax Soymilk Jelée parfait	Salad bar Italian dressing Five-bean salad Spiral noodle salad Pea soup	^*^Garbanzo à la king Fresh fruit or vegetables
Wednesday	^*^Kamut/barley cereal Beans and greens Walnuts Ground flax Soymilk ^*^Jelée parfait	Gado gado Savory tofu Steamed breadfruit cubes Bean and barley soup	^*^Papaya or pumpkin stew Fresh fruit or vegetables
Thursday	^*^Oatmeal ^*^Crunchy granola Ground flax Beans and greens Soymilk Jelée parfait	Salad bar Creamy dill dressing Sesame crackers “Eggless” egg salad Hummus Lentil soup	^*^Chili Fresh fruit or vegetables
Friday	^*^Creamy barley cereal ^*^Easy beans/greens Walnuts Ground flax Soymilk Jelée parfait	Not provided	Not provided
**WEEK 2**			
Monday	Not provided	Salad bar Yam, black bean, and greens salad with balsamic vinaigrette Cabbage soup	^*^Garbanzo kelel ^*^Cabbage salad Fresh fruit
Tuesday	^*^Apple raisin muesli Ground flax Easy beans/greens Soymilk Jelée parfait	Salad bar Thousand Island dressing Rice and lentil salad Black bean and corn soup	^*^Ma stew Fresh fruit or vegetables
Wednesday	^*^Creamy barley cereal Walnuts Ground flax Beans and greens Soymilk ^*^Jelée parfait	Salad bar Sesame dressing Thai noodle salad Oriental cabbage salad Eggplant black-eyed pea soup	^*^Tofu or vegetable stir fry ^*^Long beans in black bean sauce Fresh fruit or vegetables
Thursday	^*^Multigrain cereal Ground flax Beans and greens Soymilk Jelée parfait	Tropical haystacks (rice, pinto beans, lettuce/cabbage, peppers, peanuts, coconut, and pineapple) Golden sauce Pumpkin ginger soup	^*^Lentil loaf ^*^Mushroom gravy ^+^Roasted vegetables Fresh fruit or vegetables
Friday	^*^Scrambled tofu with peppers, onions, and greens Easy oat burgers Jelée parfait	Not provided	Not provided

* *Recipes prepared by participants*.

+ Recipes demonstrated to participants

**Table 3 T3:** Study menus for weeks 3–12.

	**Tuesday dinner**	**Thursday dinner**
Week 3	Green salad ^+^Balsamic vinaigrette ^*^Creole ^+^Barley	Promotion night Finger food provided by Diabetes Wellness Center, including breadfruit wedges, and taro squares
Week 4*(standard version only)*	Green salad ^*^Thousand Island dressing ^*^Vegetable and bean stew	Green salad ^+^Italian dressing ^*^Pasta primavera ^+^Spicy roasted chickpeas
Week 5	Potluck and/or games night (all groups)	^*^Red lentil soup ^*^Mexi dip ^+^Pita wedges Raw vegetables ^+^Banana bread
Week 6*(standardversion only)*	Cucumber salad Wet pumpkin curry Brown rice ^+^Banana ice cream	Green salad Balsamic vinaigrette ^*^Bean burger ^+^Whole-wheat bread or rolls
**ONCE-A-WEEK DINNER**		
Week 7	Green salad ^+^Tahini dressing ^*^African stew ^+^Barley	
Week 8	Green salad Italian dressing ^*^Polynesian beans and vegetables ^*^Polynesian fruit bars	
Week 9	Asian salad Sesame or ginger dressing ^*^Tofu triangles with mushrooms ^*^Brown rice	
Week 10	Papaya salad ^+^Coconut mayonnaise ^*^Stewed beans ^*^International greens ^*^Cornbread	
Week 11	Green salad ^+^Creamy dill dressing ^*^Tamale pie ^+^Brownie bars or banana carob cake	
Week 12	Green salad ^+^Oil and vinegar dressing ^*^Sweet and sour tofu Brown rice ^+^Peru pudding	

*The menus for weeks 3–12 were the same for both the standard and enhanced versions of the intensive lifestyle intervention, with the exception that the weeks 1 and 2 menus were used for weeks 4 and 6, respectively, of the enhanced version of the intervention*.

* *Recipes prepared by participants*.

+ *Recipes demonstrated to participants*.

#### Diet

The dietary intervention was adapted from the NEWSTART® program (67), a plant-based diet used by the Guam Seventh-day Adventist Clinic Wellness Center, and from concepts presented in the book *Defeating Diabetes* (69). (NEWSTART® stands for Nutrition, Exercise, Water, Sunshine, Temperance, Air, Rest, and Trust in divine power.) The diet used in this trial was mostly plant-based and emphasized whole plant foods, high fiber intake (roughly 35 g fiber per 1,000 kcal), low fat intake (20–25% of energy intake), moderate protein intake (10–15% of energy intake), and moderate sodium intake (< 2,400 mg/day) while encouraging local cuisine (70). The diet was designed to be high in phytochemicals and antioxidants, low in dietary oxidants, and to have a low glycemic load. Concentrated fats and oils were minimized, and only fat from healthy sources was permitted. Saturated fat was limited to < 7% of caloric intake, and no trans fatty acids were permitted. The diet included sufficient omega-3 fatty acids sourced from plants (primarily ground flaxseeds and walnuts), and fish, for those who chose to include it at home after the 2-week intensive phase of the intervention.

In the first 2 weeks of the dietary intervention (the intensive phase), participants consumed a 100% plant-based diet that minimized ground grains (e.g., flour, pasta, bread) and refined carbohydrates (e.g., refined sugar and starches). Also during the intensive phase, participants consumed 12 meals/week that were prepared for them by the DWC's Wellness Kitchen (see menus in Table 2), and they were instructed not to eat any outside food or snacks the remainder of those days. After the 2-week 100% plant-based phase, participants were allowed to consume boiled, steamed, or grilled fish or seafood if desired, and they continued to eat a smaller number of meals provided by the DWC (see Tables 2, 3).

When not eating meals prepared by the DWC, participants were counseled to make healthy food choices on their own using a tiered food classification system, with foods classified into four groups: 1st, 2nd, 3rd, and 4th classes (Table 4). Participants were encouraged to eat freely from the 1st class, moderately from the 2nd class, and sparingly from the 3rd class, and to completely avoid items in the 4th class. The food classification system encouraged participants to eat mostly first-class foods (75–100% of daily calories), which were defined as unprocessed, whole plant foods. To maximize nutrient density and reduce glycemic load, the first class category emphasized non-starchy vegetables, legumes, and foods rich in viscous fiber (e.g., ground flaxseed, psyllium, oats, barley, beans, and some vegetables and fruits, such as sweet potatoes, local pumpkin, turnips, and citrus fruits). Second-class foods—defined as minimally processed products such as non-dairy milks, meat substitutes, canned vegetables, and whole grain flour products—were permitted but used less often. Third-class foods included moderately processed foods, such as processed whole grains (e.g., flaked and puffed cereals) and white flour products, and animal products with moderate fat content. Fish that was not fried was permitted after the intensive phase of the program, and non-fish animal products—such as poultry, eggs from local chickens, and lower-fat dairy—were permitted, but participants were encouraged to minimize consumption of these foods. Fourth-class foods—such as beverages with added sugar, processed meat, fried foods, fast foods, and confections—were prohibited. Within all food categories, lower glycemic index foods were selected. For example, barley was emphasized in the grain group, as it has the lowest glycemic index of all grains. Portions of concentrated carbohydrate foods such as whole grains and starchy vegetables were controlled, and portion sizes of very high-fat foods such as nuts, seeds, and coconut were small to help keep calories controlled.

**Table 4 T4:** Tiered food classification system.

	**1ST CLASS FOODS: Whole Plant Foods (75–100% of calories)**	**2ND CLASS FOODS: Lightly Processed Foods and Low-Fat Animal Products (≤25% of calories)**	**3RD CLASS FOODS: Moderately Processed Foods and Mid-Fat Animal Products (≤10% of calories)**	**4TH CLASS FOODS: Heavily Processed Foods and High-Fat Animal Products (≤5% of calories)**
Vegetables	Green leafy vegetables Non-starchy vegetables: broccoli, carrots, cauliflower, onions, cucumbers, egg plant, peppers, mushrooms, tomatoes, sprouts Starchy vegetables: potatoes, sweet potatoes, corn, winter squash	Green leafy vegetables that are canned or cooked in oil	Battered vegetables Vegetables in high-fat sauces	Vegetable chips French fries Deep-fried potatoes or sweet potatoes
Protein foods	Legumes: beans, lentils, peas	Tofu Tempeh Fish (not fried)	Lean meat Poultry (no skin) Eggs Fish canned in oil	Processed or canned meat (e.g., bacon, sausage, cold cuts, frankfurters) High-fat meat Poultry Fried meat
Grains and cereal	Whole grains: barley, rye, kamut, spelt, brown rice, quinoa Cut and rolled grains	Slightly processed whole-grain breads and cereals (incl. whole wheat or other whole grain flour)	Moderately processed grains (e.g., granola bars, white flour, pasta, bagels, white rice)	Heavily processed, white flour products (e.g., donuts, cookies, and other sweet baked goods) Corn chips
Fruit	Fresh, dried, and frozen fruit	Lightly processed fruits (e.g., canned fruit in natural juice)	Fruit canned in syrupFruit juice	Fruit jams and jellies Fruit-flavored punch and drinks
Dairy/dairy alternatives	Fresh pressed nut and seed milks	Soymilk (unsweetened or original) Other commercial non-dairy milk (almond, hemp, rice)	Non- or low-fat dairy products (incl. skim or low-fat milk and cheese)	High-fat dairy products (e.g., whole milk, cream, cheese, ice cream, sour cream, whipping cream)
Higher fat whole foods, fats, and oils	Nuts, seeds and their butters (natural) Avocados Olives	Nuts and seeds with small amounts of added oil or salt Nut butters with sugar or salt	Vegetable oils Zero trans-fat margarines Nut butters with hydrogenated fats Nuts with fat, sugar, and salt	Lard Shortening Butter Hydrogenated margarine
Other			Natural sweeteners (e.g., maple syrup, blackstrap molasses, honey, brown rice syrup)	Refined sugar (e.g., white sugar, syrup) Soda Sugar-sweetened beverages Candy

#### Exercise

Participants were asked to exercise at least 30–60 min per day throughout the study, which included both solo exercise and structured group exercise classes that decreased in intensity as the study proceeded (Table 1). The structured group exercise included culturally acceptable physical activities as determined by focus groups. Group exercise included walking, calisthenics, elastic-band resistance training, Marshallese-style dance classes, and use of gym equipment, such as treadmills, cardio gliders, rowing machines, and free weights. During the 2-week intensive phase of the intervention, participants attended a 1-h group exercise class 4 days per week and completed 2 daily walks on their own, with one before breakfast and one after lunch. They also completed one daily walk as a group after dinner. Each after-meal walk was 10–20 min. On non-clinic days, participants exercised solo. They were encouraged to exercise at the clinic when possible, and when not possible, they were asked to use their therabands and to exercise for at least 30–60 min at home. After the 2-week intensive phase, participants attended 60-min exercise group classes on clinic days and were counseled to exercise on their own on non-clinic days. They were also advised to continue with their daily walks (including 10–20 min walks after each meal) and to attend group fitness classes (such as dance classes).

#### Stress Management

Participants in the intervention group were also provided with stress counseling and management activities, such as deep breathing, stretching, and words of encouragement. They were provided a lecture on suggestions for handling stressful situations and getting support.

#### Cultural Adaptation

The intervention was delivered in a culturally-sensitive manner by trained indigenous Marshallese and Canvasback Missions staff. Prior to designing the intervention, Canvasback Missions had more than 20 years of experience working with the Marshallese people and government, including operating NEWSTART lifestyle programs. The intervention was designed in partnership with the RMI MOH. The study team met with the MOH and health care providers to determine the appropriate level of content and preferred methods of learning. Consequently, the program was structured to be interactive and rely on active learning. All Canvasback Missions staff were provided with significant cultural sensitivity training that included instruction in the cultural traditions and local customs of respect. Marshallese staff were hired, trained, and performed as many study functions as possible, including meal preparation and group activities. Training included a trip to Guam to learn the NEWSTART program before coming back to Majuro to set-up the study. We also engaged local physicians, nurses, dance instructors, and our staff cooks to be a part of education sessions, in an effort to make the program culturally relevant. This was supported by strong relationships that were forged with Marshallese and American dignitaries, the MOH personnel, community group leaders, and store managers. Study documents, lectures, and instructions were provided in the Marshallese language. To tailor the dietary intervention, recipes from Marshallese cuisine were incorporated and adapted while still ensuring that the diet was plant-based and met nutritional targets. Finally, group exercise activities were led by a Marshallese staff member who was known in the community for leading such activities, and local dance routines were encouraged as aerobic activity.

### Measurements and Outcomes

#### Assessments

Study assessments included demographics, anthropometrics, vital signs, serum cardiometabolic risk factors, medication usage, and behavioral assessments. All study assessments were performed at weeks 0, 2, 6, 12, and 24 unless otherwise stated below.

#### Anthropometrics and Vital Signs

Height, weight, waist circumference, blood pressure, and resting heart rate were all measured in duplicate using standard procedures. Height was measured using a stadiometer and was used to tabulate BMI. Waist circumference was measured at the level of the umbilicus above the iliac crest.

#### Medications

To monitor changes in glucose levels in the intervention group and adjust medication dosages accordingly, a glucometer was used during the first 2 weeks and fasting labs at weeks 2, 6, and 12 were relied on thereafter. Medication dosages were adjusted by participants' primary care physicians and/or the DWC clinicians. Medications and their dosages were recorded at each assessment. Changes in the average number of medications and in the percentage of participants taking one or more medications will be compared across groups for both all medications and diabetes-specific medications.

#### Glucometers

Participants in the intervention group were given glucometers during the intensive 2-week phase of the intervention to measure their glucose levels, as needed. These assessments were used both for educational purposes and to make medication adjustments.

#### Dietary Assessment

Participants completed a food frequency questionnaire at baseline (week 0) and at week 24. The questionnaire was tailored to Majuro residents and asked participants about the frequency with which they consumed 110 food items, as well as the typical serving size and any seasonal differences in consumption (for fresh fruits and vegetables only). Participants also described what they usually ate for breakfast, lunch, dinner, and snacks. Participants also completed a one-page, self-reported diet quality assessment at weeks 2, 6, and 12 to report any changes in food intake, including the foods they now avoid, eat less of, and eat more of. Changes in dietary intake and other lifestyle factors were used to help gauge the program's effectiveness. At the end of the trial, participants also self-reported their adherence to the diet using a 1–5 Likert scale.

#### Physical Activity Assessment

Cardiopulmonary fitness was assessed at each time point using the Harvard step test in year 1 and both the Harvard step test and the timed 1-mile walk in year 2. For the Harvard step test, participants stepped up onto a gym bench ~20 inches in height once every 2 s for 5 min or until the participant could not maintain the pace. Thereafter, they were seated in a chair, and their pulse was assessed 1, 2, and 3 min after completing the step tests, and fitness level was graded as 50 × (duration in seconds)/(sum of the three post-exercise heart rates). For the timed 1-mile walk test, potential participants were given pedometers to wear and were asked to walk a one-mile roadway loop outside the hospital at a pace they could maintain without running or stopping. Participants were instructed to walk alone at their own pace. After the individuals returned, their walking time and steps were collected and recorded. Physical activity levels were assessed by self-report using a modified version of the International Physical Activity Questionnaire at each time point and through weekly pedometer readings**. **All participants—including those in the control group—were asked to wear pedometers throughout the study and report their step count on a weekly basis. Participants came to the DWC to report their readings or, if they were unable to come in, called study staff to report their readings.

#### Safety

Participants were instructed to report adverse events as soon as they occurred and were also queried about adverse events at each assessment. To minimize the risk of complications from exercises, warm-up exercises were used to gently increase the intensity of the physical activity.

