The management of adverse events and data collection in a country with no prior research infrastructure presented the greatest challenges to the trial. The main challenge for adverse event management was adjusting medication dosages downwards to avoid hypoglycemic reactions in the intervention group. When participants were not in the clinic, they often had to return to their family physician to adjust their medication dosages, which meant long wait times and a fee. This was particularly problematic for participants on insulin, who had to be very carefully monitored so that insulin dosages could be reduced or stopped accordingly. Further, because medication dosing tended to increase for control subjects and decrease for intervention subjects, future reported outcomes will likely be biased toward the null hypothesis. We also faced problems with missing data due to participants not showing up for appointments, procedural failures by the laboratory, and the hospital being new to the extensive documentation requirements for clinical trials, in a country where clinical trials have never been performed before. It took several trips and digging through boxes of duplicate lab slips to fill in missing logbook entries. The positive outcome is that new policies and reporting procedures were established for any future lab work that may be required, and all lab work that was done is now backed up. To tackle the challenge of participant attendance at clinic visits, research staff attempted to reach every participant by phone, and in some cases, went to the participant's home or work to remind them of the importance of the blood draws and measures to complete the study. We have discovered that within the RMI, more effort is needed than in the U.S. to ensure that participants fully participate in the intervention.

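### Adverse events are described as actively queried only at weeks 0, 2, 6, 12 and 24, while early staff contact and glucometers favour one arm, so hypoglycaemia may be detected unequally in weeks 1-12

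*Protocol article*

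**What the plan says.** The Safety section of the protocol article describes two routes for adverse events, with no distinction by arm: "Participants were instructed to report adverse events as soon as they occurred and were also queried about adverse events at each assessment". The Assessments section fixes the schedule: "All study assessments were performed at weeks 0, 2, 6, 12, and 24 unless otherwise stated below". No other active query is described.

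Contact with staff outside the assessments differs by arm at first. Under Lifestyle Intervention, in the opening two weeks "participants in all cohorts attended 5–6 h/day of group classes on Mondays–Thursdays (4 days/week) at the DWC". The enhanced version (Cohorts 3-5) repeats that intensity in weeks 4 and 6. The remaining weeks up to week 6 have two clinic days each. In weeks 7-12, "participants in all cohorts participated in a 4–5 h once per week session". In weeks 13-24, "no instruction or counseling was provided, and participants came to the center weekly to turn in their pedometer readings".

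On home glucose measurement, the Glucometers section says: "Participants in the intervention group were given glucometers during the intensive 2-week phase of the intervention to measure their glucose levels, as needed". No glucometer is described for controls.

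One contact is common to both arms. Under Physical Activity Assessment all participants, controls included, "were asked to wear pedometers throughout the study and report their step count on a weekly basis", at the centre or by telephone.

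The Discussion identifies the event of most concern: "The main challenge for adverse event management was adjusting medication dosages downwards to avoid hypoglycemic reactions in the intervention group". It adds that medication dosing tended to rise in controls and fall in the intervention arm, and that some participants missed appointments.

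**The concern.** Spontaneous reports depend on opportunity and prompting. A participant who spends hours with study staff several days a week, and who can see a low reading on a meter, has more chance of having an episode recognised and recorded than one whose scheduled contact is a weekly step count. The event at issue is one that a meter can reveal and that may be brief. If recorded events from all sources are compared between arms, the difference mixes true risk with intensity of surveillance.

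The likely direction is more recorded hypoglycaemia in the intervention arm in weeks 1-12. Usual care could then look safer than it was, even though dosing in controls tended to increase and they are not described as having meters. The biases that the Discussion does consider (contamination of controls, medication changes) do not include this one.

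A separate weakness affects both arms. In the second half of follow-up, anything a participant does not volunteer depends on recall over 12 weeks at a single visit.

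**Working it through.** The plan states no figure for adverse-event detection, so there is none to reproduce. The check is arithmetic on the visit schedule and on the contact schedule in Table 1 and the Lifestyle Intervention text.

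**Gaps between active queries** (Assessments, Safety)
- Query weeks: 0, 2, 6, 12, 24.
- Differences: 2 − 0 = 2; 6 − 2 = 4; 12 − 6 = 6; 24 − 12 = 12 weeks.
- Weeks 13-24 are 12 of 24 weeks, half of follow-up, with one query at the end.

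**Scheduled contact days, weeks 1-12** (weeks × days per week)
- Intervention, standard version: 2×4 (weeks 1-2) + 4×2 (weeks 3-6) + 6×1 (weeks 7-12) = 8 + 8 + 6 = 22.
- Intervention, enhanced version: 4×4 (weeks 1, 2, 4, 6) + 2×2 (weeks 3, 5) + 6×1 (weeks 7-12) = 16 + 4 + 6 = 26.
- Control: 12×1 weekly step reports = 12.

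The assessments are common to both arms and are left out of all counts. I assume that the intervention arm hands in its step counts on clinic days; if those were separate contacts, the imbalance would be larger.

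| Period | Intervention | Control | Ratio |
|---|---|---|---|
| Weeks 1-2 | 8 | 2 | 4.0 |
| Weeks 1-12, standard | 22 | 12 | 22/12 = 1.8 |
| Weeks 1-12, enhanced | 26 | 12 | 26/12 = 2.2 |
| Weeks 13-24 | 12 | 12 | 1.0 |

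The table counts days, not hours. An intervention clinic day is several hours with staff, while a control contact may be a telephone call.

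**Glucometers**: one arm, 2 of 24 weeks.

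**How unequal detection carries through.** Let the true risk p be equal in both arms, and let the probabilities that an event is recorded be s1 (intervention) and s0 (control). The observed risk ratio is (p × s1)/(p × s0) = s1/s0, so p cancels. The detection values below are assumed and are not in the documents.

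| s1 | s0 | Observed ratio when the true ratio is 1 |
|---|---|---|
| 0.9 | 0.9 | 1.00 |
| 0.9 | 0.7 | 1.29 |
| 0.9 | 0.5 | 1.80 |

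This shows only that a difference in detection passes one-for-one into the observed ratio. It does not estimate the bias in this trial.

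**The case against.** The strongest reply is that this is a two-sentence safety summary in a condensed article. Forms, scripts and source coding belong in the full protocol, and rules for analysing adverse events belong in an analysis plan; neither is shown. Nothing in the Safety section is wrong or contradicted elsewhere. Adverse events are not among the primary or secondary endpoints, and the Statistical Analyses section does not say that events from different sources will be pooled. More contact in one arm is also inherent in an open-label trial of an intensive programme.

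Most of that stands, and it limits the point. The absence of a fuller procedure is not a finding. What remains is the schedule that is stated, and the one-arm contact and meters set beside it.

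Four stronger readings are tempting, and the text does not support them.
- *Events were collected only at the five assessments.* Spontaneous reporting ran in both arms throughout. For the same reason, events in someone who missed week 24 are not necessarily lost.
- *The 12-week gap disadvantages one arm.* Scheduled contact is equal in weeks 13-24. The inequality is early; the late weakness is shared.
- *The weekly step report carried no safety question.* The article describes none, which is silence and not a statement that none was asked.
- *Hypoglycaemia was under-detected.* The Discussion describes difficulty in managing doses and does not report missed events.

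It is also fair to say that restricting a comparison to the scheduled queries is no cure. A low meter reading in week 1 can be recalled at the week 2 query, and the restriction can drop events already reported to staff, mostly in the intervention arm.

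**Conclusion.** The concern holds in limited form. The described method gives the arms unequal opportunity for detection in weeks 1-12: about twofold in scheduled contact days, fourfold in weeks 1-2, with meters in one arm for those two weeks. Hypoglycaemia may therefore be recorded unequally early on. After week 12 the arms are alike, and both depend on self-report plus one late query.

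The contact ratios follow from the printed schedule and assume that it was kept. The effect on recorded event rates is a reasoned possibility whose size cannot be derived from the documents. It bears on the safety comparison and not on the method for assessing glycaemic efficacy. It is worth acting on because a contact common to both arms already existed and could have carried the same questions.

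**What to change.** **In the Safety section, for this design or a successor:** attach one fixed set of adverse-event and hypoglycaemia-symptom questions to the weekly pedometer report made by both arms, whether in person or by telephone. Record the source of each event: weekly question, scheduled assessment, spontaneous report, clinic session or glucometer.

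**For this trial's data:** the last cohort began in July 2008, so questioning cannot be added. Report events by source where it was recorded, and say so where it was not. Show the between-arm comparison for the week 2, 6, 12 and 24 queries beside the all-source comparison, since neither is free of bias alone. State that early surveillance was more intense in the intervention arm.

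**Cost:** prospectively, a few minutes per weekly contact and one extra form field. Retrospectively, one additional tabulation and a sentence on the limitation; the common-query comparison will contain fewer events.
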